### 12.1.11 MANAGEMENT OF RENAL TOXICITY

|                                                                                                                                           |                                                                                                                                                                                                                                                                                                                                                                                                                                                                                                                                                    |
|-------------------------------------------------------------------------------------------------------------------------------------------|----------------------------------------------------------------------------------------------------------------------------------------------------------------------------------------------------------------------------------------------------------------------------------------------------------------------------------------------------------------------------------------------------------------------------------------------------------------------------------------------------------------------------------------------------|
| Nephritis (graded according to creatinine increased), grade 2 : creatinine $>1.5 - 3.0 \times$ baseline or $>1.5 - 3.0 \times$ ULN | 

• Withhold pembrolizumab

• Continue evorpacept (ALX148) and cetuximab, or may hold at investigator's discretion

• Administer corticosteroids (prednisone 1 to 2 mg/kg or equivalent) followed by tapera-c

• Monitor changes of renal function

• If event improves to <math>\leq</math>Grade 1 or baseline, resume evorpacept (ALX148), cetuximab, and pembrolizumab. Pembrolizumab is resumed at fixed dose. Dose reductions of evorpacept (ALX148) and

 |
|-------------------------------------------------------------------------------------------------------------------------------------------|----------------------------------------------------------------------------------------------------------------------------------------------------------------------------------------------------------------------------------------------------------------------------------------------------------------------------------------------------------------------------------------------------------------------------------------------------------------------------------------------------------------------------------------------------|

|                                                                                                                                                                                                      |                                                                                                                                                                                                                                                                                                                                  |
|------------------------------------------------------------------------------------------------------------------------------------------------------------------------------------------------------|----------------------------------------------------------------------------------------------------------------------------------------------------------------------------------------------------------------------------------------------------------------------------------------------------------------------------------|
|                                                                                                                                                                                                      | cetuximab are not required but can be considered upon discussion with the medical monitor. a-c                                                                                                                                                                                                                        |
| Nephritis (graded according to creatinine increased), grade 3 or 4

Nephritis, grade 3: creatinine >3.0 x baseline or >3.0 - 6.0 x ULN

Nephritis, grade 4: creatinine >6.0 x ULN | 
 
• Permanently discontinue evorpacept (ALX148), cetuximab, and pembrolizumab. Permanently discontinue study treatments
 
• Administer corticosteroids (prednisone 1 to 2 mg/kg or equivalent) followed by tapera
 
• Monitor changes of renal function
 
 |

a. If corticosteroids have been initiated, they must be tapered over  $\geq 1$  month to  $\leq 10$  mg/day oral prednisone or equivalent before pembrolizumab can be resumed. Add prophylactic antibiotics for opportunistic infections.

b. The acceptable length of the extended period of time for which pembrolizumab can be held to allow for corticosteroids to be reduced to  $\leq 10$  mg/day oral prednisone or equivalent must be agreed upon by the investigator and the Medical Monitor.

c. Resumption of pembrolizumab may be considered in patients who are deriving benefit and have recovered from the immune-related event (baseline or Grade  $\leq 1$ ). Patients can be rechallenged with pembrolizumab only after approval has been documented by both the investigator (or an appropriate delegate) and the Medical Monitor.

### 12.1.12 MANAGEMENT OF HEMOPHAGOCYTIC LYMPHOHISTIOCYTOSIS

Hemophagocytic lymphohistiocytosis (HLH) is a syndrome of excessive immune activation that can result in life-threatening tissue destruction. Manifestations include the following diagnostic criteria (the presence of at least 5 of 8 criteria are suggested to satisfy the diagnosis):

- Fever  $\geq 38.5^{\circ}\text{C}$
- Splenomegaly
- Peripheral blood cytopenia, with at least two of the following: hemoglobin  $< 9$  g/dL, platelets  $< 100,000/\text{microL}$ ; absolute neutrophil count  $< 1000/\text{microL}$
- Hypertriglyceridemia (fasting triglycerides  $> 265$  mg/dL) and/or hypofibrinogenemia (fibrinogen  $< 150$  mg/dL)
- Hemophagocytosis in bone marrow, spleen, lymph node, or liver
- Low or absent NK cell activity
- Ferritin  $> 500$  ng/mL
- Elevated soluble CD25 (soluble IL-2 receptor alpha [sIL-2R]) two standard deviations above age-adjusted laboratory-specific norms

Additional manifestations of HLH can include pulmonary abnormalities (such as hypoxia or consolidation or ground-glass opacities on imaging), neurologic abnormalities (such as ataxia, seizures, or mental status changes), liver function and coagulation abnormalities, hypotension, renal dysfunction, skin manifestations, and bleeding.

HLH has been reported to occur in patients receiving immune checkpoint inhibitors including in <1% of patients administered pembrolizumab (reference USPI Keytruda). Suggested treatment guidelines are based on these reports, as well as the HLH-94 protocol.

HLH is not included in NCI CTCAE 5.0, so grading is based on the term “Immune system disorders - Other, specify”:

| Event                                                                                                                                                                                                                                                            | Guidance                                                                                                                                                                                                                                                                                                                                                                                                                                                                                                                                                                                                                                                                                                                                                                                                                                                                                                                                                                                      |
|------------------------------------------------------------------------------------------------------------------------------------------------------------------------------------------------------------------------------------------------------------------|-----------------------------------------------------------------------------------------------------------------------------------------------------------------------------------------------------------------------------------------------------------------------------------------------------------------------------------------------------------------------------------------------------------------------------------------------------------------------------------------------------------------------------------------------------------------------------------------------------------------------------------------------------------------------------------------------------------------------------------------------------------------------------------------------------------------------------------------------------------------------------------------------------------------------------------------------------------------------------------------------|
| Grade 1: Asymptomatic or mild symptoms; clinical or diagnostic observations only; intervention not indicated                                                                                                                                                     | 
 
Obtain the following evaluation: CBC, CMP (including total, direct, and indirect bilirubin), LDH, haptoglobin, reticulocyte count, folate, B12, iron studies, peripheral smear, urinalysis, PT/INR, PTT, autoimmune serology, direct agglutinin testa, fibrinogen, D-dimer, GGT, triglycerides, ferritin, NK cell activity, soluble IL-2 receptor alpha (soluble CD25), CXCL9, interferon gamma, TNF alpha, IL-6, IL-10, and IL-12b
 
Obtain study tubes for PK, PD, and ADA (see Section 8.2.6)
 
CT scan of the chest, abdomen, and pelvis
 
Continue evorpaccept (ALX148), cetuximab, and pembrolizumab at the same doses
 
Continue with standard monitoring guidelines
 
                                                                                                                                                                                                               |
| Grade 2: Moderate; minimal, local or noninvasive intervention indicated; limiting age-appropriate instrumental ADL                                                                                                                                               | 
 
Permanently discontinue study treatments
 
Obtain evaluation as listed in Grade 1, including laboratories, study tubes, and CT scan
 
Obtain tissue biopsy of the bone marrow, lymph node, or liver if feasible
 
Do not wait on diagnostic confirmation to start treatment. Administer 1 mg/kg/d prednisone equivalents, followed by ≥ 1-month taper. Monitor blood work at least weekly until the steroid tapering process is complete.
 
                                                                                                                                                                                                                                                                                                                                                                                                                                                                              |
| 
Grade 3: Severe or medically significant but not immediately life threatening; hospitalization or prolongation of existing hospitalization indicated; limiting self care ADL
 
Grade 4: Life-threatening consequences; urgent intervention indicated
 | 
 
Permanently discontinue study treatments
 
Admit the patient to the hospital
 
Obtain evaluation as listed in Grade 1, including laboratories, study tubes, and CT scan
 
Obtain tissue biopsy of the bone marrow, lymph node, or liver if feasible
 
Do not wait on diagnostic confirmation to start treatment. Administer methylprednisolone 1 gram daily x3 days. Then, prednisone (or equivalent) minimum dose 1 mg/kg for at least one week, per investigator discretion. Then, gradual taper over at least 8 weeks total, per investigator discretion
 
Monitor blood work at least weekly until the steroid tapering process is complete
 
Steroids are the suggested primary treatment. Additional immunosuppressive medications (such as tocilizumab or the HLH-94 protocolc) may be added at the discretion of the investigator and in consultation with the medical monitor
 
 |

- a. Because evorpaccept (ALX148) binds to CD47 expressed on red blood cells (RBC), the presence of evorpaccept (ALX148), which contains a modified IgG1 Fc domain, in patient whole blood and plasma can interfere with cross-matching assays performed by blood banks in order to identify compatible or least incompatible units of RBC for transfusion. Both the direct antibody test (DAT) and the indirect antibody test (IAT) may appear to be positive for reactive antibodies (IgG) in samples from patients who are on treatment with evorpaccept

## 12.2 APPENDIX 2: PROTOCOL CRITERIA FOR MEASUREMENT OF STUDY EFFICACY ENDPOINTS (RECIST V1.1 AND IRECIST)

### 1 Definitions

1.1 Evaluable for adverse events. All patients will be evaluable for adverse event evaluation from the time of their first treatment.

1.2 Evaluable for response. All patients who have received at least one cycle of therapy and have their disease re-evaluated will be considered evaluable for response (exceptions will be those who exhibit objective disease progression prior to the end of cycle 1 who will also be considered evaluable). Patients on therapy for at least this period and who meet the other listed criteria will have their response classified according to the definitions set out below.

Response and progression will be evaluated in this study using the revised international criteria (1.1) proposed by the RECIST (Response Evaluation Criteria in Solid Tumors) committee as well as the modified iRECIST guidelines. Investigators should note the different requirements for confirmatory scans as well as follow up for the two criteria.

See section 4.1.2 for criteria for continuing treatment past RECIST 1.1 disease progression.

### 2 RECIST 1.1 Response and Evaluation Endpoints

**2.1 Measurable Disease.** Measurable tumor lesions (nodal, subcutaneous, lung parenchyma, solid organ metastases) are defined as those that can be accurately measured in at least one dimension (longest diameter to be recorded) as  $\geq 20$  mm with chest x-ray and as  $\geq 10$  mm with CT scan or clinical examination. Bone lesions are considered measurable only if assessed by CT scan and have an identifiable soft tissue component that meets these requirements (soft tissue component  $\geq 10$  mm by CT scan). Malignant lymph nodes must be  $\geq 15$  mm in the short axis to be considered measurable; only the short axis will be measured and followed. All tumor measurements must be recorded in millimeters (or decimal fractions of centimeters). Previously irradiated lesions are not considered measurable unless progression has been documented in the lesion.

**2.2 Non-measurable Disease.** All other lesions (or sites of disease), including small lesions are considered nonmeasurable disease. Bone lesions without a measurable soft tissue component, leptomeningeal disease, ascites, pleural/pericardial effusions, lymphangitis cutis/pulmonis, inflammatory breast disease, lymphangitic involvement of lung or skin and abdominal masses followed by clinical examination are all non-measurable. Lesions in previously irradiated areas are non-measurable, unless progression has been demonstrated.

**2.3 Target Lesions.** When more than one measurable tumor lesion is present at baseline all lesions up to a maximum of 5 lesions total (and a maximum of 2 lesions per organ) representative of all involved organs should be identified as target lesions and will be recorded and measured at baseline. Target lesions should be selected on the basis of their size (lesions with the longest diameter), be representative of all involved organs, but in addition should be those that lend themselves to reproducible repeated measurements. Note that pathological nodes must meet the criterion of a short axis of  $\geq 15$  mm by CT scan and only the short axis of these nodes will contribute to the baseline sum. All other pathological nodes (those with short axis  $\geq 10$  mm but  $< 15$  mm) should be considered non-target lesions. Nodes that have a short axis  $< 10$  mm are considered non-pathological and should not be recorded or followed (see 8.2.4). At baseline, the sum of the target lesions (longest diameter of tumor lesions plus short axis of lymph nodes: overall maximum of 5) is to be recorded.

After baseline, a value should be provided on the eCRF for all identified target lesions for each assessment, even if very small. If extremely small and faint lesions cannot be accurately measured but are deemed to be present, a default value of 5 mm may be used. If lesions are too small to measure and indeed are believed to be absent, a default value of 0 mm may be used.

**2.4 Non-target Lesions.** All non-measurable lesions (or sites of disease) plus any measurable lesions over and above those listed as target lesions are considered non-target lesions. Measurements are not required but these lesions should be noted at baseline and should be followed as “present” or “absent”.

## 2.5 Response.

All patients will have their BEST RESPONSE from the start of study treatment until the end of treatment classified as outlined below:

Complete Response (CR): disappearance of target and non-target lesions and normalization of tumor markers. Pathological lymph nodes must have short axis measures <10 mm (Note: continue to record the measurement even if <10 mm and considered CR). Residual lesions (other than nodes <10 mm) thought to be non-malignant should be further investigated (by cytology specialized imaging or other techniques as appropriate for individual cases before CR can be accepted).

Partial Response (PR): at least a 30% decrease in the sum of measures (longest diameter for tumor lesions and short axis measure for nodes) of target lesions, taking as reference the baseline sum of diameters. Non target lesions must be non-PD.

Stable Disease (SD): Neither sufficient shrinkage to qualify for PR nor sufficient increase to qualify for PD taking as reference the smallest sum of diameters on study.

Progressive Disease (PD): at least a 20% increase in the sum of diameters of measured lesions taking as references the smallest sum of diameters recorded on study (including baseline) AND an absolute increase of  $\geq 5$  mm. Appearance of new lesions will also constitute progressive disease (including lesions in previously unassessed areas). In exceptional circumstances, unequivocal progression of non-target disease may be accepted as evidence of disease progression, where the overall tumor burden has increased sufficiently to merit discontinuation of treatment or where the tumor burden appears to have increased by at least 73% in volume. Modest increases in the size of one or more non-target lesions are NOT considered unequivocal progression. If the evidence of PD is equivocal (target or non-target), treatment may continue until the next assessment, but if confirmed, the earlier date must be used.

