### Secondary Objectives:

1. To determine the disease-control rate (DCR), defined as stable disease, partial response, or complete response with evorpacept (ALX148), cetuximab, and pembrolizumab using RECIST v1.1
2. To determine the duration of response (DOR) with evorpacept (ALX148), cetuximab, and pembrolizumab, defined as the time from response (partial or complete) to progression using RECIST v1.1 or death from any cause
3. To determine the progression-free survival (PFS) with evorpacept (ALX148), cetuximab, and pembrolizumab, defined as the time from enrollment to the first observation of progression using RECIST v1.1 or death from any cause
4. To determine the overall survival (OS) with evorpacept (ALX148), cetuximab, and pembrolizumab, defined as the time from enrollment to death from any cause
5. To determine the first cycle dose-limiting toxicities (DLT) of evorpacept (ALX148), cetuximab, and pembrolizumab in stage 1
6. To evaluate the safety and tolerability of evorpacept (ALX148), cetuximab, and pembrolizumab, defined and graded according to the NCI CTCAE v5.0

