#### **4.1.2 CRITERIA FOR CONTINUATION OF TREATMENT BEYOND RECIST V1.1- DEFINED PROGRESSION**

In all cohorts, at the time of RECIST v1.1-defined progression (i.e., iUPD), treatment is permitted to continue until the next assessment (at least 4 weeks but no longer than 8 weeks later) if the following criteria are met:

- Patient is clinically stable (An assignment of clinical stability requires that no worsening of performance status has occurred, that no clinically relevant increases in disease-related symptoms such as pain or dyspnea occur that are thought to be associated with disease progression (these symptoms are generally understood to mean a requirement for increased palliative intervention), and that no requirement for intensified management of disease-related symptoms exists, including increased analgesia, radiotherapy, or other palliative care.)
- Absence of tumor progression at critical anatomical sites (e.g., leptomeningeal disease) that cannot be managed by protocol-allowed medical interventions
- Patient and investigator agree to continue treatment

- Patient signs the Treatment Beyond Progression Informed Consent Form
- If the subsequent scan continues to show progression, all therapy will be discontinued and the patient will be taken off study.

At least 28 days and no more than 35 days after discontinuation of treatment, patients will return to undergo the listed activities in Schedule of Events (section 1.3, unless already completed in the last week, or last 6 weeks for response assessment). Patients continuing to experience toxicity at this point following discontinuation of treatment will continue to be followed at least every 4 weeks until resolution or determination, in the clinical judgment of the Investigator, that no further improvement is expected. If the patient has any concern and contacts the clinic, the patient will be seen in the clinic within 5 calendar days of the patient's contact with the clinic (assessments will be the same as the assessments performed at the Final Study/Treatment Discontinuation Visit). Overall survival information will be collected via telephone calls and/or clinic visits every 3 months  $\pm$  14 days (first call and/or clinic visit to occur 3 months following the Final Study/Treatment Discontinuation Visit) until death, withdrawal of consent, the patient is lost to follow-up, study termination by AGICC, or a maximum of 2 years from the Final Study/Treatment Discontinuation Visit.

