If iUPD is noted, a follow-up scan should be obtained at least 4 weeks but no longer than 8 weeks later. Schedule of tumor assessments are independent of any changes to the study treatment administration schedule (e.g., dose delay) and may occur mid-cycle depending on length of cycle. If a tumor assessment must be performed early or late, subsequent assessments should be conducted according to the original schedule based on the date of first study drug administration (Cycle 1, Day 1). Confirmation of response (PR or complete response [CR]) will be done no earlier than 28 days from study entry. In the case of SD, measurements must have met the SD criteria at least once after study entry at a minimum interval not less than 6 weeks. Patients who discontinue study treatment for any reason other than disease progression will continue to undergo tumor response evaluations (approximately every 9 weeks) until progressive disease. Rising tumor markers (e.g., CEA) in the absence of radiological evidence of progression is not considered progressive disease.

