#### **9.4.2 ANALYSIS OF THE PRIMARY EFFICACY HYPOTHESIS & STOPPING CRITERIA**

The one-sided proportion test will be conducted for ORR against the null hypothesis that the ORR is less than or equal to 3%, with significance level of 0.05. The cumulative frequency, estimated proportion, and the exact 95% confidence intervals will be reported. A sample size of 48 achieves 87% power if the ORR is 15% using a one-sided exact test with a target significance level of 0.05. These results assume that the ORR of the historical control is 3%.

For  $\alpha = 0.025$  (1-sided) and power of 87%, MinMax design supports stopping enrollment for futility as noted if there are no responses (partial response or complete response as defined in the protocol) in first 24 subjects. Otherwise, full study enrollment will proceed as planned. Using a Simon-like 2-stage design, ORR will be determined based on the first 24 evaluable patients (including patients in both Stage 1 and Stage 2). If there are no responses (partial response or complete response as defined in the protocol) in the first 24 evaluable patients, then study enrollment will be stopped for futility. If there is at least one response (partial response or complete response as defined in the protocol) in the first 24 evaluable patients then full study enrollment will proceed as planned. If there are no responses (partial response or complete response as defined in the protocol) in the first 23 evaluable patients then enrollment will be temporarily paused to allow response evaluation of the 24th evaluable patient after up to 15 total weeks (ie 5 total cycles) of study therapy. If the 24th patient has response (partial response or complete response as defined in the protocol) then then full study enrollment will proceed as planned. If the 24th patient does not have a response (partial response or complete response as defined in the protocol) then the study will be stopped for futility. See Section 9.4.2 for statistical considerations.

---

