| PR                                                                                                                                                                                                                                                                                                                                                                                                                                                                                                                                                                                  | Non-PD/ not all evaluated | No          | PR               |                                                      |
| SD                                                                                                                                                                                                                                                                                                                                                                                                                                                                                                                                                                                  | Non-PD/ not all evaluated | No          | SD               | Documented at least once ≥4 wks. from baseline       |
| Not all evaluated                                                                                                                                                                                                                                                                                                                                                                                                                                                                                                                                                                   | Non-PD                    | No          | NE               |                                                      |

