## 5 Response and Stable Disease Duration (RECIST 1.1 and iRECIST)

Response duration will be measured from the time measurement criteria for CR/PR or iCR/iPR (whichever is first recorded) are first met until the first date that recurrent or progressive disease is objectively documented, taking as reference the smallest measurements recorded on study (including baseline).

Stable disease duration will be measured from the time of start of treatment until the criteria for progression are met, taking as reference the smallest sum on study (including baseline).

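### Appendix 2 conflicts with the protocol's own definitions of DOR and stable disease, and leaves RECIST 1.1 best response open past first progression

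*Protocol*

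**What the plan says.** **DOR.** Secondary objective 2 in Section 3 (and the synopsis, Section 1.1) has DOR "defined as the time from response (partial or complete) to progression using RECIST v1.1 or death from any cause". Appendix 2 item 5, which covers RECIST 1.1 and iRECIST together, runs it "until the first date that recurrent or progressive disease is objectively documented" and does not mention death.

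**Stable disease.** Section 8.1, repeated in footnote 20 of the schedule of events, says that "measurements must have met the SD criteria at least once after study entry at a minimum interval not less than 6 weeks". Table 4 of Appendix 2 instead asks for "Documented at least once ≥4 wks. from baseline". Both the length and the starting point differ.

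**Best response.** Appendix 2 item 2.5, in the RECIST 1.1 part, states: "All patients will have their BEST RESPONSE from the start of study treatment until the end of treatment classified as outlined below". Section 4.1.2 says that at RECIST 1.1 progression, and under listed conditions, "treatment is permitted to continue until the next assessment (at least 4 weeks but no longer than 8 weeks later"). Section 8.1 adds that "Patients who discontinue study treatment for any reason other than disease progression will continue to undergo tumor response evaluations", about every 9 weeks until progression.

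**The concern.** Appendix 2 is titled as the protocol's criteria for measuring the efficacy endpoints, and the futility rule counts responses as the protocol defines them. Its wording therefore decides who is a responder, who has disease control and when a response ends.

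- A responder who dies without documented progression has a DOR event under Section 3 and no end date under item 5. If an analyst follows item 5 and censors that death, DOR is too long.
- The same early scan can establish stable disease under Table 4 and fail to do so under Section 8.1. Stable disease feeds the disease control rate (DCR), which is tested against 45%.
- The best-response window follows treatment, not disease. It stays open for a patient treated past RECIST progression. It closes for a patient who stops drug for toxicity without progressing, although that patient is still scanned. The first case could add a response to the RECIST ORR that belongs only to iRECIST and so blur the planned comparison of the two criteria; the second drops a genuine RECIST response. ORR is the primary efficacy endpoint, and a single response among the first 24 evaluable patients decides whether enrollment goes on.

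**Working it through.** **1. Reproduce the plan's ORR figure.** Inputs from Section 9.4.2: N = 48, null 3%, alternative 15%, one-sided exact test at 0.05. The claim is "A sample size of 48 achieves 87% power if the ORR is 15% using a one-sided exact test". With X binomial(48, p):

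- P(X ≥ 4 | p = 0.03) = 0.0555, above 0.05, so 4 responses are not enough.
- P(X ≥ 5 | p = 0.03) = 0.0143, so the cut-off is 5 of 48. The 0.025 level in the same section gives the same cut-off.
- P(X ≥ 5 | p = 0.15) = 0.8656, which reproduces the stated 87%.
- With the stop at 0 of 24 built in, these become 0.0140 and 0.8598.

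**2. Best response.** The documents give no rate of RECIST response after RECIST progression. I assume that counting such responses adds e percentage points to the 3% null, and recompute P(X ≥ 5 | 48, 0.03 + e), ignoring the futility stop, and the chance of passing the interim look, 1 − (1 − 0.03 − e)^24:

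- e = 0: 1.4% false positive; 51.9% pass the interim look
- e = 1 point: 4.2%; 62.5%
- e = 2 points: 9.1%; 70.8%
- e = 3 points: 15.9%; 77.3%

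Timing does not rule the case out at the interim look. The 24th patient may be followed for up to 15 weeks. Progression at the week-9 scan puts the follow-up scan at weeks 9 + 4 = 13 to 9 + 8 = 17, so part of that range falls inside the 15 weeks.

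**3. DOR.** Expected responders under the alternative are 0.15 × 48 = 7.2, so one such death is about one in seven DOR outcomes. As an illustration, assume exponential times, a true median of 6.0 months (not a protocol figure), and a share q of DOR events that are deaths without progression. Censoring them inflates the median by 1/(1 − q):

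- q = 5%: 6.0/0.95 = 6.3 months
- q = 10%: 6.0/0.90 = 6.7 months
- q = 20%: 6.0/0.80 = 7.5 months

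**4. Stable disease.** Scans are due every 9 weeks ± 5 days. The first falls between (63 − 5)/7 = 8.3 and (63 + 5)/7 = 9.7 weeks, later than both the 4-week and the 6-week minimum, so the two rules agree at every scheduled scan. They can differ only when an unscheduled scan, which Section 8.1 allows if progression is suspected, shows stable disease before week 6 and progression follows by the first scheduled scan. The DCR design itself reproduces: at 28 of 48, alpha is 0.0438 under 45% and power is 0.8680 under 65%, matching the stated 87%.

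**The case against.** The strongest reply is that little of this can reach the results.

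**Best response.** Treatment normally ends at RECIST progression. Going beyond it needs clinical stability and a separate consent, and lasts only to the next scan. Table 4 makes any new lesion progression whatever the target lesions do, and item 2.5 bars a PR while non-target disease is progressing. What remains is mainly progression by target-lesion growth that then shrinks to at least 30% below baseline. Permission to assign a response after progression is written only in the iRECIST part. All of this stands and makes the route narrow. It does not close it, because nothing in item 2.5 ends the RECIST window at first progression.

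A reader might infer that item 2.5 contradicts Sections 3 and 8.1. It does not: neither sets a best-response window. A reader might also argue that one credited response turns the 5-of-48 rule into 4 of 48, taking the type I error from 1.4% to 5.6%. That assumes exactly one such response in every trial run under the null, which the documents do not support. Nor do they support a claim that ORR is biased upward: losing responses seen off treatment lowers it, and the net direction is unknown.

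**DOR.** Section 3 states the endpoint, item 5 is a general measurement rule that never says deaths are censored, and DOR is secondary and unpowered. This limits the consequence, but the two texts still give different end points.

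**Stable disease.** Because baseline imaging may be 28 days before Cycle 1 Day 1, it is tempting to say that Table 4 allows stable disease on the first day of treatment. The schedule has no tumor assessment on that day, so this is not a realistic case.

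**Conclusion.** The point holds as two contradictions and one badly fixed window.

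- DOR: a direct contradiction on death. The bias is upward if deaths without progression are censored; its size depends on how many there are, which the protocol does not say.
- Stable disease: a direct contradiction on interval and time origin. The effect on DCR is nil at scheduled scans and arises only through early scans done for suspected progression.
- RECIST best response: a defective cut-off for the primary efficacy endpoint that can err in both directions. The 4.2% to 15.9% range rests wholly on the assumed 1 to 3 extra points. At 1 point the error stays below 0.05 but exceeds the 0.025 that Section 9.4.2 also names.

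The stated sample size and power for ORR and DCR reproduce and are not in question. The text is worth correcting because so few responses decide both the interim look and the final test.

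**What to change.** Make three edits in Appendix 2:

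1. Item 2.5: classify RECIST 1.1 best response from the start of study treatment to the first RECIST 1.1 progression, including scans made after treatment has stopped but before progression. Count any later response under iRECIST only.
2. Item 5: end response duration at recurrence, progression or death from any cause, as Section 3 already does.
3. Table 4: replace the stable-disease entry with the interval and time origin of Section 8.1, at least 6 weeks after study entry.

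The rules on treatment beyond progression are not affected. No new data are needed, since the scans and deaths are already collected, and no stated N, alpha or power changes. The observed ORR may move up or down. Median DOR may be shorter than under item 5 as it stands. DCR changes only if an early unscheduled scan would have counted.
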